#### Enrolment process

A suitable time for enrolment is the 30-day follow-up after rectal cancer surgery. It is not mandatory to document the screening process, and the degree of screening may vary between participating centers (Fig. 1). Patients will be asked to participate by the surgeon responsible for the follow-up visit, will be given information, will sign a written consent, and will be given an enrolment number.

**Fig. 1 Fig1:**
[figure not shown]
Flow chart of the study

#### CRF (Case Report Form)

Operation day: protocol will be filled out in connection with the operation and the operating notes blinded according to instruction.30-day follow-up: patient questionnaire filled out by patient and protocol will be filled out by another doctor than the operating surgeon.1-year and 3-year follow-up (in connection with cancer control): patient questionnaire and results from the CT scan.

### Sample size

Retrospective studies have shown a cumulative incidence of hernia between 7.4 and 23% after loop ileostomy reversal [16, 17, 19–21]. The reduction of hernia is described to be reduced up to 5.5 times [26] with a synthetic mesh and twice with a biological mesh [30]. We estimate a baseline cumulative hernia incidence of 12% and a triple reduction in hernia frequency using synthetic mesh. Some 208 patients (104 in each arm) are required in order to detect a reduction of hernia occurrence from 12 to 3% when using a double-sided *t-*test, a p-value of 0.05, and 80% power. We are planning to add 10% to compensate for loss to follow- up.

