**Methods:**

The present multicenter, double-blinded, randomized, controlled study will compare standard suture closure of the abdominal wall in loop ileostomy reversal with retromuscular synthetic mesh at the stoma site. The study has been approved by the Regional Ethical Review board in Stockholm.

Patients aged 18–90 years, operated on with low anterior resection and a protective loop ileostomy for rectal cancer and planned for ileostomy reversal, will be considered for inclusion in the study. Randomization will be 1:1 on the operation day with concealed envelopes. The estimated sample size is intended to evaluate the superiority of the experimental arm and to detect a reduction of hernia occurrence from 12 to 3%. The operation method is blinded to the patients and in the chart and for the observer at the 30-day follow-up. The main outcome is hernia occurrence at the stoma site within 3 years postoperatively, diagnosed through CT with strain. Secondary outcomes are operation time, length of hospital stay, pain, and 30-day complications.

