## Introduction

### Background and rationale

Rectal cancer is a common form of cancer worldwide, with an age-standardized incidence rate of 14.4–16.6 per 100,000 for men in Europe, Eastern Asia, and Australia [1]. A temporary protective loop ileostomy is widely used when operating rectal cancer with low anterior resection [2–5]. The purpose of this practice is to reduce the impact of possible anastomotic leakage, but the method is constantly under debate because of its complications [6]. Ostomies can reduce the quality of life by causing leakage, parastomal hernia, and prolapse [7–11].

A temporary ostomy is reversed in a separate operation. One complication in connection with stoma closure is the development of a hernia at the former stoma site. A hernia is a weakening of the layers of the abdominal wall [12], which may cause pain and discomfort, but also more serious complications such as obstructed or strangulated bowel. The incidence of hernia after ostomy closure varies between 7 and 35% [13–20], whilst in studies including only ileostomy reversal, the hernia incidence was 7–15% [16, 17, 19–21].

The best method to avoid hernia after stoma closure is unknown. Most commonly, surgeons close the aponeurosis in one layer with a monofilament suture [20]. The use of prophylactic mesh in the abdominal wall has been tried in smaller non-randomized studies [22–24]. A meta-analysis from 2021 including both ileo- and colostomies showed a reduction in hernia incidence from 18.1 to 7.8% with no increase in complications using different types of reinforcing mesh [25]. In a retrospective study from 2018, the use of synthetic mesh reduced the incidence of hernia from 17.2 to 1% [24].

In a retrospective comparative study reviewing only the closure of ileostomies, the hernia incidence was reduced from 36.1 to 6.4% with a synthetic onlay mesh [26]. A multicenter study, randomizing loop ileostomy reversal between biological mesh and standard closure, showed significantly lower proportions of stoma site hernia, 12% vs 20%, in the mesh group, without increasing the complication rate [27].

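### The sample size section assumes a threefold reduction but computes for a fourfold one, and with the stated two-sided test 104 per arm gives 80% power for neither (about 57% and 70%)

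*Protocol article*

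**What the plan says.** The Sample size section gives the assumed effect in words: "We estimate a baseline cumulative hernia incidence of 12% and a triple reduction in hernia frequency using synthetic mesh". The next sentence gives it in figures. It says that "Some 208 patients (104 in each arm) are required" to "detect a reduction of hernia occurrence from 12 to 3" percent, and names a double-sided t-test, with "test, a p-value of 0.05, and 80% power". A further 10% is to be added for loss to follow-up. The Methods part of the abstract repeats the figures ("to detect a reduction of hernia occurrence from 12 to 3" percent) and does not use the word triple.

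The same section measures reductions as ratios of incidence. It credits synthetic mesh with a reduction of up to 5.5 times, citing the study of which Background and rationale says "the hernia incidence was reduced from 36.1 to 6.4% with a synthetic onlay mesh"; 36.1/6.4 = 5.6.

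**The concern.** Two adjacent sentences give two design effects, and the larger one carries the calculation. On the section's own usage, "a triple reduction in hernia frequency using synthetic mesh" means 12% to 4%, whereas 12% to 3% is fourfold. The design effect fixes what the 80% refers to and how a non-significant result should be read. The article states that the sample size is adequate both under Strengths and limitations and in the Discussion. If power for the effect described in words is well below 80%, a null result could be taken as evidence against mesh when the trial had little better than an even chance of detecting that effect. Rewording alone might seem enough, so it also has to be checked whether 104 per arm gives 80% power for 12% v 3%.

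**Working it through.** **Inputs (Sample size section).** Control incidence 12%; mesh incidence 4% (words) or 3% (figures); 104 per arm; two-sided alpha 0.05; power 80%. Allocation is 1:1 (Trial design). Normal quantiles: 1.960 (two-sided 5%), 1.645 (one-sided 5%), 0.842 (80% power).

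**Step 1: the effects.** 12/3 = 4.0 (fourfold) and 12/4 = 3.0 (threefold).

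**Step 2: reproduce the stated 104 per arm for 12% v 3%.** With unpooled variance,

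n = (z_alpha + z_beta)² × [p1(1−p1) + p2(1−p2)] / (p1−p2)².

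- Variance sum: 0.12×0.88 + 0.03×0.97 = 0.1056 + 0.0291 = 0.1347. Squared difference: 0.09² = 0.0081.
- Two-sided, as stated: 7.849 × 0.1347/0.0081 = 130.5, so 131 per arm. Other two-sided methods give 134 (pooled variance), 132 (t-test), 122 (arcsine) and 155 (continuity-corrected). None gives 104.
- One-sided 5%: 6.183 × 0.1347/0.0081 = 102.8, so 103 per arm; 105 with pooled variance.

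The stated 104 therefore matches a one-sided 5% calculation and not the two-sided one described.

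**Step 3: two-sided power at 104 per arm.** With the pooled variance under the null,

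power = Φ{[(p1−p2) − 1.960 × √(2p̄(1−p̄)/n)] / √([p1(1−p1) + p2(1−p2)]/n)}, where p̄ is the mean of p1 and p2.

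- 12% v 3%: p̄ = 0.075; null SE = √(0.13875/104) = 0.03653; alternative SE = √(0.1347/104) = 0.03599. Power = Φ[(0.09 − 0.07159)/0.03599] = Φ(0.512) = 69.6%.
- 12% v 4%: p̄ = 0.08; null SE = √(0.1472/104) = 0.03762; alternative SE = √(0.1440/104) = 0.03721. Power = Φ[(0.08 − 0.07374)/0.03721] = Φ(0.168) = 56.7%.

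**Step 4: sensitivity to method.**

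| Method (two-sided 5%, 104 per arm) | 12% v 3% | 12% v 4% |
|---|---|---|
| Pooled | 69.6% | 56.7% |
| Unpooled | 70.6% | 57.5% |
| t-test (the test named) | 70.2% | 57.1% |
| Arcsine | 73.6% | 59.4% |
| Exact power, chi-square | 73.0% | 59.1% |
| Exact power, Fisher | 63.5% | 48.5% |

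No method reaches 80% for either effect.

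**Step 5: split the shortfall (pooled).** One-sided power for 12% v 3% is 79.7%. Moving to the stated two-sided test costs 79.7 − 69.6 = 10.1 points. Moving from 3% to 4% costs a further 69.6 − 56.7 = 12.9 points. In the other order (one-sided power for 12% v 4% is 68.7%), the effect mismatch costs 11.0 points and the sidedness 12.0.

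**Step 6: size for 80% two-sided power.** 134 per arm for 12% v 3% and 180 per arm for 12% v 4% (pooled), against 104.

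**The case against.** The strongest reply is that the operative target is not in doubt. The fall from 12% to 3% is given numerically in both the abstract and the Sample size section, it is the only effect to which 80% power is attached, and the article nowhere claims 80% power for 12% v 4%. On this view triple is one loosely chosen word. Much of that stands, and writing fourfold is an acceptable way to settle the wording. It does not rescue the power statement, because 12% v 3% has only about 70% two-sided power at 104 per arm.

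A reader might infer that the word triple alone takes power from 80% to 57%. The documents do not support that: about 10 of the 23 points are lost before the 4% target enters, because the sample size does not match the stated two-sided test.

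A reader might also infer that even a threefold effect is optimistic, since the randomised trial of biological mesh "showed significantly lower proportions of stoma site hernia, 12% vs 20%, in the mesh group" (1.7-fold) and the meta-analysis fell from 18.1% to 7.8% (2.3-fold). Neither is specific to synthetic mesh. The synthetic-mesh figures in the same section are larger: 36.1% to 6.4%, and 17.2% to 1%. Those studies are retrospective and can fairly be doubted, but the document does not show a threefold effect to be too large.

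Finally, the 10% added for loss to follow-up could raise power if nobody were lost. With about 115 evaluable per arm (208 × 1.1 = 229 in total), two-sided power is about 61% for 12% v 4% and 74% for 12% v 3%, still short of 80%.

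**Conclusion.** The contradiction stands: the words give 12% to 4% and the figures give 12% to 3%. The stated 80% power is wrong as written for both. The chance of missing a true effect is about 43% for the threefold reduction and 30% for the fourfold one, against the 20% stated. These figures assume 104 evaluable patients per arm, a control incidence of 12%, a two-sided 5% comparison of two independent proportions, and triple read as a ratio of incidences, as the section's own use of times implies. That 104 came from a one-sided calculation is an inference from the close match (103 to 105 per arm); the document does not say so.

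**What to change.** Make the words and the figures in the Sample size section state one design effect: either fourfold, 12% to 3%, or threefold, 12% to 4%. The abstract needs changing only if the second is chosen, since it already says 12% to 3%.

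Under either choice, replace the 80% with the two-sided power of 104 per arm for that effect: about 70% for 12% v 3%, or about 57% for 12% v 4%. Report both values, so that a non-significant result is read against the power the trial had. Changing triple to fourfold while leaving 80% in place would correct the wording and keep a false power statement.

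The cost is a few words and a less favourable stated power. No outcome data are needed to make the change.

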## Strengths and limitations of this study

This is to our knowledge the only randomized controlled study to investigate synthetic mesh to prevent hernia after loop ileostomy closure.The primary outcome of hernia will be measured objectively and is clinically relevant and important to patient and physician alike.The trial is double-blind.The planned sample size is adequate to evaluate the superiority of the intervention arm.

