## Discussion

This double-blinded randomized controlled study will compare the use of retromuscular synthetic mesh during the closure of loop ileostomy to standard care. The sample size is adequate to evaluate the superiority of the experimental arm. If this study can show a lower frequency of hernia with the use of prophylactic mesh, it may lead to new surgical guidelines during stoma closure.

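### 104 patients per arm do not give 80% power for 12% v 3% with a two-sided 5% test; the power is about 70%, and 104 is what a one-sided test would need

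*Protocol article*

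**What the plan says.** The Sample size section gives a complete set of inputs and a result:

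- Effect and number: "Some 208 patients (104 in each arm) are required in order to detect a reduction of hernia occurrence from 12 to 3" per cent.
- Test: "when using a double-sided" t-test, that is, two-sided.
- Error rates: "a p-value of 0.05, and 80% power".
- A further 10% is to be added for loss to follow-up.

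The Trial design section gives 1:1 allocation and a superiority framework. The Interim analyses section plans none, so no adjustment of alpha is involved. The article nowhere mentions a one-sided test or another significance level.

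Two other places rely on this calculation. Strengths and limitations says: "The planned sample size is adequate to evaluate the superiority of the intervention arm". The Discussion says: "The sample size is adequate to evaluate the superiority of the experimental arm".

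**The concern.** For event rates of 12% and 3%, 104 per arm is too few for a two-sided 5% test with 80% power, and it is close to the number for a one-sided 5% test. If the calculation was one-sided and the report two-sided, the design lacks the power claimed for its primary outcome.

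What is at stake is how the result is read. The Discussion says that a positive result may lead to new surgical guidelines. A non-significant result would be read as coming from a trial with a 1 in 5 chance of missing the planned effect, when that chance is about 3 in 10. Readers could then take it as stronger evidence against the mesh than it is.

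**Working it through.** **Inputs**, all from the article: p1 = 0.12, p2 = 0.03, difference 0.09, alpha 0.05, power 80%, 1:1 allocation, 104 per arm. Then p1(1−p1) + p2(1−p2) = 0.1056 + 0.0291 = 0.1347, the mean rate is 0.075, and 2 × 0.075 × 0.925 = 0.13875. Normal quantiles: 1.960 (two-sided 5%), 1.645 (one-sided 5%), 0.842 (80% power).

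**1. Trying to reproduce 104 per arm as stated (two-sided).**

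- Unpooled variance: n = (1.960 + 0.842)² × 0.1347 / 0.09² = 130.5, so 131.
- Pooled variance under the null: n = (1.960 × √0.13875 + 0.842 × √0.1347)² / 0.09² = 133.3, so 134.
- Two-sample t-test (noncentral t, SD = √(0.1347/2) = 0.2595): 131.5, so 132.
- Arcsine: 122. With continuity correction: 155.

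No two-sided method gives 104.

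**2. The same formulas, one-sided 5%.**

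- Unpooled: (1.645 + 0.842)² × 0.1347 / 0.0081 = 102.8, so 103.
- Pooled: 104.9, so 105.
- t-test: 103.5, so 104. Power is 79.8% at 103 per arm and 80.2% at 104.

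The one-sided version of the test that the protocol names gives exactly the published number.

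**3. Two-sided power at 104 per arm.** The unpooled standard error of the difference is √(0.1347/104) = 0.03599, and 0.09/0.03599 = 2.501. Power is Φ(2.501 − 1.960) = Φ(0.541) = 70.6%.

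| Method (two-sided 5%, 12% v 3%) | Power, 104 per arm | Power, 115 per arm |
|---|---|---|
| z, unpooled | 70.6% | 74.8% |
| z, pooled | 69.6% | 73.9% |
| t-test | 70.2% | 74.5% |
| Arcsine | 73.6% | 77.8% |
| Chi-square, uncorrected, exact enumeration | 73.0% | 77.8% |
| Fisher's exact, exact enumeration | 63.5% | 66.9% |

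**4. The 10% addition.** 208 × 1.10 = 228.8, about 229 patients or 115 per arm. The right-hand column shows power if every one of them were evaluable. It stays below 80% for every method.

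**5. What 104 per arm can detect.** With two-sided 5%, 80% power and 12% in the control arm, the mesh arm would have to be at about 2.2% (2.2% unpooled and t-test, 2.1% pooled).

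**The case against.** The case on the other side does not dispute that the stated inputs fail to give 104. It makes five points.

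- *The one-sided origin is not documented.* True. It is an inference from an exact match. The error does not depend on it, because 104 is wrong for the stated inputs whatever its source.
- *A single figure of 70% hides the spread between methods.* Fair. The range is 63.5% to 73.6%, and the required size falls to 122 per arm by the arcsine formula. All of these still miss the claim.
- *The shortfall is smaller once the 10% addition is counted.* With no losses, the most favourable methods reach about 78%. But the protocol reserves that addition for loss to follow-up. The outcome needs CT at 1 and 3 years in patients treated for cancer, and data will not be imputed, so no loss at all is unlikely.
- *The planned analysis is not a t-test.* The Statistical methods section names paired tests, a Kaplan-Meier model and possible regression adjustment. Power under those could differ somewhat, but the sample size statement names its own test and fails for that test.
- *The effect size itself is unsettled.* The same section assumes "a baseline cumulative hernia incidence of 12% and a triple reduction in hernia frequency using synthetic mesh". A threefold reduction from 12% is 4%, whereas 12% to 3% is fourfold. This stands as a separate inconsistency, and it makes matters worse: at 12% v 4% the two-sided requirement is 180 per arm, and power at 104 per arm is about 57% (both by the pooled formula). The 70% is therefore the more favourable reading.

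**Conclusion.** The concern holds. For 12% v 3% with a two-sided 5% test, 80% power needs about 131 to 134 evaluable patients per arm (262 to 268 in all), against the stated 104 (208). At 104 per arm the power is about 70% and the type II error about 30%.

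This rests only on the rates, alpha, sidedness and allocation that the protocol states, and on an unpaired comparison of two proportions with 104 evaluable patients in each arm. That the number came from a one-sided calculation is very likely but not proven. The point must be fixed, because it misstates the main design property of the primary outcome and two claims of adequacy depend on it.

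**What to change.** Settle first whether the intended effect is 12% to 3% or a threefold reduction, since the power figure depends on it. If 12% to 3% stands, replace the power statement in the Sample size section with wording such as: *104 evaluable patients per arm give about 70% power (two-sided 5%) to detect 12% v 3%; 80% power would need about 131 to 134 per arm; the reduction detectable with 80% power is from 12% to about 2.2%.* In Strengths and limitations and in the Discussion, remove the claim that the sample size is adequate, or qualify it with the 70% figure.

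The restatement costs wording only and needs no extra patients. The price is a less favourable stated power. If the sponsor prefers to keep the 80% claim, the cost is patients: 131 to 134 evaluable per arm, which is 54 to 60 more in total than 208 (262 − 208 and 268 − 208), before any allowance for loss. Trial status gives December 2024 as the preliminary end of recruitment, so restating the power is the smaller change.

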#### Exclusion criteria

Language barrier or cognitive disabilityRecurrent inoperable cancer (patients with operable metastasis are not excluded)Large parastomal hernia not suitable for standard closure

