#### Criteria for discontinuing or modifying allocated interventions

The following situations resulting in discontinuation may arise:A patient may have been inadequately enrolled, not meeting the eligibility criteria. This patient should be excluded from data analysis and only reported in the flow chart.If a patient dies or is lost to follow-up, the data can be used until the date of the last follow-up.If a patient withdraws from the study, the study data collected until this point will be used.

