### Outcomes

#### Primary outcome

The primary outcome is a hernia at the former stoma site at any time point during the 3-year study follow-up. Hernia will be diagnosed through CT abdomen with and without strain, performed 1 and 3 years after cancer surgery. A patients’ questionnaire will be run at the same time.

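### The 10% allowance names only loss to follow-up; about 229 patients yield the required 208 only if loss, death and exclusion together stay at or below 9.2%

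*Protocol article*

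**What the plan says.** The Sample size section of the protocol article states: "Some 208 patients (104 in each arm) are required in order to detect" "a reduction of hernia occurrence from 12 to 3"%, with a two-sided test at 0.05 and 80% power. It then says "We are planning to add 10% to compensate for loss to" follow-up. It gives no total to be randomised, no expected loss rate and no mention of deaths.

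The section on criteria for discontinuing or modifying allocated interventions lists death and loss as two events ("If a patient dies or is lost to follow-up") and lets their data count up to the last follow-up. It also takes patients who were wrongly enrolled out of the data analysis.

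The Primary outcome section counts a hernia at any time in the 3-year follow-up, from CT scans "performed 1 and 3 years after cancer surgery". Patients may be up to 90 years old. Recurrent inoperable cancer is excluded, but "patients with operable metastasis are not excluded". The statistical methods compare incidence at 1 and 3 years and add a Kaplan-Meier model, and missing data are not imputed. Both the Strengths and limitations section and the Discussion call the sample size adequate.

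**The concern.** The allowance is given one purpose, loss to follow-up. Two other routes by which a randomised patient can lack the 3-year outcome appear elsewhere in the same document: death, and removal for ineligibility. Some deaths before the last scan are foreseeable in this population. If the 10% is used up by loss alone, nothing is left for them.

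At stake is how far the number with a complete primary outcome may fall below the number that the plan says it requires, and whether the two adequacy statements can stand without that number being shown.

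**Working it through.** **Inputs from the protocol.** Required number 208 (104 per arm); 12% v 3%; two-sided 0.05; 1:1 allocation; 10% added.

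**Input not in the protocol.** The proportion who die before the last scan. I assume 5, 10, 15 or 20% of those randomised, for illustration only.

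**Step 1: the plan's base figure.** I used the normal approximation for two proportions with pooled null variance. With mean proportion 0.075 and n = 104 per arm:
- standard error under the null: √(2 × 0.075 × 0.925 / 104) = 0.0365
- standard error under the alternative: √((0.12 × 0.88 + 0.03 × 0.97) / 104) = 0.0360
- two-sided power: Φ((0.09 − 1.96 × 0.0365) / 0.0360) = Φ(0.51) = 69.6%

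A t-test calculation gives 70.2%. The stated 80% is not reproduced. A two-sided test needs 134 per arm. A one-sided 5% test needs 105 per arm and has 79.7% power at 104, so 208 corresponds to a one-sided test. This is a separate error, but every two-sided power below starts from it.

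**Step 2: the allowance.**
- Total: 208 × 1.10 = 228.8, so 229.
- Largest total attrition that still leaves 208: (229 − 208) / 229 = 9.2%.
- At 10% loss and nothing else: 229 × 0.90 = 206.1. Two-sided power is 69.2%, which is 0.4 points below that at 208.
- Dividing instead of adding: 208 / 0.90 = 231.1, so 232 in two equal arms, 3 more than 229.

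**Step 3: assumed deaths on top of 10% loss.** Evaluable = 229 × (1 − 0.10 − f × d), where d is the assumed death proportion and f is the share of deaths that leave no usable outcome.

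| Assumed deaths d | Evaluable, f = 1 | Two-sided power | Evaluable, f = 0.5 | Two-sided power |
|---|---|---|---|---|
| 5% | 195 | 67% | 200 | 68% |
| 10% | 183 | 64% | 195 | 67% |
| 15% | 172 | 61% | 189 | 65% |
| 20% | 160 | 58% | 183 | 64% |

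The f = 1 columns are the worst case. Compounding loss and death instead of adding them gives 196, 185, 175 and 165 evaluable at f = 1, with power 67, 65, 62 and 59%. Exclusions for ineligibility would come off any of these counts; the documents give no figure for them.

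**The case against.** Several points on the other side are sound.

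- **Adding versus dividing is immaterial.** It costs 2 to 3 patients and 0.4 points of power. The protocol never says that 10% is the expected loss rate, and it speaks only of some 208 patients.
- **Not every death is a lost outcome.** A hernia on the 1-year CT counts as an event even if the patient later dies. A patient without one contributes follow-up to that scan in the Kaplan-Meier analysis.
- **The exposure may be shorter than 3 years.** The Primary outcome section times the scans from cancer surgery, and randomisation comes later, at stoma reversal. Patients with recurrent inoperable cancer are excluded.
- **The wording could be loose.** Death and loss share one sentence and the same handling, so the 10% may have been meant as general attrition.

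These points limit the size of the problem but do not remove it. The sample size was set for two cumulative proportions, incidence at 3 years is compared directly, and nothing is imputed. A patient who is free of hernia at year 1 and dies before the last scan has no 3-year status and says nothing about hernias arising after the first scan. If the 10% was meant to cover everything, the text should say so, and the ceiling is still 9.2%.

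A reader might infer that the trial will fail to deliver 208 evaluable patients. The documents do not support that. A shortfall of any size depends on a death rate that they do not give, and total attrition of 9.2% or less would deliver 208. Nor should the gap between about 69% and the stated 80% be put down to attrition, since most of it comes from the base number.

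**Conclusion.** The allowance is incomplete as worded, and the adequacy statements rest on a number of evaluable patients that the protocol never derives. The certain part is small: about 229 patients yield 208 only with total attrition of at most 9.2%, and 10% loss alone leaves 206.

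The larger part is conditional. With deaths assumed at 5 to 20%, on top of 10% loss, two-sided power is 2 to 6 points below the 70% at 208 if half the deaths are non-evaluable, and 3 to 11 points below if all are. These figures assume 12% v 3%, equal arms, the normal approximation and no credit for partial follow-up in the non-evaluable patients. The drop from 80% to about 70% at 208 belongs to the base number, and correcting the allowance would not repair it.

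**What to change.** In the Sample size section, state:
1. the total to be randomised;
2. one overall attrition proportion covering loss, death and exclusion for ineligibility, which attrition data pooled over both arms, without breaking the blind, can supply;
3. the number expected to have the primary outcome, as total × (1 − attrition);
4. the two-sided power at that number.

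Then align the adequacy statements in the Strengths and limitations section and in the Discussion with these figures. The base number should be corrected in the same revision, so that the power is quoted on one basis.

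The change needs no extra enrolment, no unblinding and no change of design. Its cost is a few restated sentences and a less favourable stated power.
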